#### Randomization and allocation procedures

Following completion of baseline questionnaires (timepoint 1), participants are randomized online between the intervention (LWL group) and care as usual control condition (CAU group). Randomization is based on a 1:1 ratio using random permuted block randomization, with block sizes of 2, 4, and 6 to ensure equal numbers of participants in each study arm. Randomization is stratified by two variables: relationship to baby (mother who carried baby vs partner) and distress severity at baseline (low distress vs moderate-to-high distress) to ensure equal distribution across both study arms. The allocation sequence was generated by a biostatistician and uploaded to the LWL course delivery system by an IT consultant, both independent to the conduct of this trial. The course delivery system is coded to randomize participants, based on the allocation sequence, immediately following completion of baseline questionnaires. The allocation sequence is concealed from the research team for the duration of the study. Once participants have been randomly allocated to a study arm, they will be automatically logged into their online participant portal and notified of group allocation on their home page. Once allocated to a study arm, both participants and research personnel will not be blinded to group allocation.

Participants in both study arms will be able to access usual care and support services during the 21-week trial period. Such care is expected to include a heterogenous mix of professional and non-professional supports and interventions, and will be assessed at each primary timepoint. Contact between participants and research personnel will be: (1) in response to participant request for technical support; (2) initiated by the trial clinician for the purpose of safety monitoring; or (3) initiated by the research team if a participant has been inactive for more than 14 days following assessment timepoints. No further outcome data will be collected for participants that withdraw or drop out. Participants are encouraged to tell their general practitioner (GP; Family Doctor) that they are participating in this research trial as part of the intervention or control study arm.

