**Methods:**

This trial is a two-arm parallel group randomized controlled trial comparing the intervention arm (LWL) with a care as usual control arm (CAU). We anticipate recruiting 150 women and men across Australia who have experienced a stillbirth or neonatal death in the past 2 years. Participants randomized to the LWL group will receive the six-module internet-based program over 8 weeks including automated email notifications and reminders. Baseline, post-intervention, and 3-month follow-up assessments will be conducted to assess primary and secondary outcomes for both arms. The primary outcome will be the change in Kessler Psychological Distress Scale (K10) scores from baseline to 3-month follow-up. Secondary outcomes include perinatal grief, anxiety, depression, quality of life, program satisfaction and acceptability, and cost-effectiveness. Analysis will use intention-to-treat linear mixed models to examine psychological distress symptom scores at 3-month follow-up. Subgroup analyses by severity of symptoms at baseline will be undertaken.

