### Participants and recruitment

An opportunity sample of self-selecting participants will be recruited via a snowball sampling strategy. Parents and healthcare professionals will be notified of this trial through online and social media advertising, flyers at local maternity services (e.g., Mater Mothers’ Hospital, Brisbane, Australia), and by word of mouth (e.g., healthcare professionals; parent support organizations). All parents interested in participating are directed to the LWL website to review participant information and express interest. This trial aims to recruit at least 75 participants in each study arm (total *N* = 150) which allows for an anticipated dropout rate of 25% (see Statistical methods). Participants will be recruited over a 12-month period.

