#### Inclusion criteria

This study will recruit parents who have experienced a stillbirth (defined as a baby that dies before birth and after 20 weeks’ gestation including termination of pregnancy for medical reasons) or neonatal death (defined as a baby that dies after birth and within 28 days) in the past 2 years and more than 8 weeks ago. Additional inclusion criteria include: aged 18 years and older; currently residing in Australia; access to a computer with Internet connection; written and oral fluency in English language; willingness to provide personal contact details (including emergency contact); and willingness to provide informed consent online.

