#### Exclusion criteria

The exclusion criteria are as follows: parents in a current pregnancy; those who have experienced an early pregnancy loss (i.e., before 20 weeks’ gestation); stillbirth or neonatal death less than eight weeks ago; or a diagnosis of psychosis, bipolar disorder, or schizophrenia within the last 2 years. Individuals who are experiencing severe symptoms of psychological distress, depression, and/or suicidal ideation at enrolment will also be excluded.

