#### Data analyses

All analyses will be undertaken in Statistical Package for the Social Sciences (SPSS) version 25 (IBM SPSS, IBM Corp., Armonk, NY, USA) using re-identifiable (i.e., coded) data. Data analysts will not be blinded to study arm. Descriptive statistics will be used to summarize participant demographic and obstetric data. Group differences in baseline variables will be examined using cross-tabulations, independent *t*-tests, and regression analyses, with differences in baseline outcome measures controlled for in further analyses. To determine program efficacy, intention-to-treat linear mixed models will be estimated for each outcome measure, with restricted maximum likelihood (REML) estimation used to account for missing data due to participant dropouts [60]. These models will yield more accurate estimates of effect compared to completer as they account for the unbalanced nature of the data [60, 61]. Mixed models will be estimated separately for each outcome variable, with time, group, and time by group interaction entered as fixed factors. Comparisons within and between groups from baseline to 3-month follow-up for each group will be undertaken for outcomes. Between-group effect sizes will be calculated using the pooled standard deviation of the estimated marginal means and adjusted for sample size (Hedges *g*). Effect sizes of 0.20, 0.50, and 0.80 are considered small, moderate, and large respectively [62]. Descriptive statistics will be used to summarize participant engagement, adherence, and program satisfaction data.

A cost-utility analysis comparing the program’s efficacy and acceptability against usual care in a primary care setting will be conducted. Analyses will be based on direct and indirect costs associated with program development, evaluation, and participants’ social opportunity costs (e.g., work productivity, absenteeism, and presenteeism). The health economic evaluation protocol and findings from this trial will be published separately.

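### Both parents of one baby can enrol and are randomised separately, so about half of such couples are expected to be split across arms, with nothing stated to detect the resulting dilution

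*Protocol article*

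**What the plan says.** All references are to the protocol article.

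- **Who may enrol.** Inclusion criteria: "This study will recruit parents who have experienced a stillbirth" or neonatal death. The abstract expects women and men. The exclusion list covers current pregnancy, early loss, recent loss, certain diagnoses and severe symptoms. Having a partner already in the trial is not on it.
- **How they are found.** Participants and recruitment: "An opportunity sample of self-selecting participants will be recruited via a snowball sampling strategy", with word of mouth among the routes.
- **How they are allocated.** Randomization and allocation procedures: "Randomization is based on a 1:1 ratio using random permuted block randomization, with block sizes of 2, 4, and 6". On the strata: "Randomization is stratified by two variables: relationship to baby (mother who carried baby vs partner"; the second variable is baseline distress (low, or moderate to high). The system allocates each person automatically once that person's own baseline is complete.
- **What the intervention contains.** Exercises can be saved or printed for later use, and Module 5 deals with how grief differs between partners and with communication.
- **How it is analysed.** Data analyses: mixed models "with time, group, and time by group interaction entered as fixed factors". The sample size section uses a within-subject correlation only. Couples, clustering and contamination between partners are not mentioned.

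**The concern.** Enrolment of both parents is foreseeable here. Partner is a randomisation stratum, reaching men is a stated aim, and recruitment spreads through personal networks. If one parent is allocated to the program and the other to usual care, the control parent can be exposed at home without ever logging in. The design withholds the program from controls until their last assessment, and a split couple defeats that intention.

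At stake is the K10 contrast. Contaminated controls move it towards zero, so a program that works could look weaker or miss significance. No model term restores the lost contrast. If couples are never identified, its extent cannot be examined either.

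**Working it through.** **1. Chance of a split.** Mother and partner are in different strata whatever their distress level, so they never share a list or a block. Each list is 1:1 and nothing links the two draws. P(split) = 0.5 × 0.5 + 0.5 × 0.5 = 0.5. Simulating the permuted-block scheme gave a mean of 0.499 to 0.500. The realised share varies: with 30 couples, the central 95% range was 33% to 67%.

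**2. Number of couples (assumed).** Let f be the share of participants enrolled together with their partner.
- Low scenario: the Background cites an earlier trial that was 92% female. If 8% of 150 are partners (12 people), all enrolled with the mother, then f = 24/150 = 0.16, and about 6 of 12 couples are split.
- High scenario: f = 0.40, which is 30 couples, about 15 of them split.

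**3. Dilution.** The share of controls with a partner in the program is f/2. Let c be the fraction of the benefit that passes to the control parent (also assumed). Then d = 0.5 × (1 − c·f/2).

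**4. The plan's own sample size.** The cited repeated-measures formula, two-sided, gives 2 × (1.96 + 0.84)² × (1 + 2 × 0.5) / (3 × 0.25) ≈ 42 per arm. That is 84 in total, or 84/0.75 = 112 after 25% dropout. The stated 150 is not reproduced. This is a separate matter. Here I take 150 enrolled and 75 × 0.75 ≈ 56 completers per arm.

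**5. Power.** For a baseline-adjusted comparison at one timepoint with ρ = 0.5, the residual SD is √(1 − 0.25) = 0.866. The noncentrality is d / (0.866 × √(2/56)) = d / 0.1637, which is 3.055 at d = 0.5. Power is from a two-sided t-test on 110 df. The last column uses the plan's repeated-measures formula (normal approximation).

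| f | c | d | Power, baseline-adjusted | Power, repeated-measures formula |
|---|---|---|---|---|
| 0 | – | 0.50 | 0.857 | 0.90 |
| 0.16 | 0.5 | 0.48 | 0.828 | 0.875 |
| 0.16 | 1 | 0.46 | 0.796 | 0.846 |
| 0.40 | 0.5 | 0.45 | 0.778 | 0.831 |
| 0.40 | 1 | 0.40 | 0.678 | 0.736 |

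**6. Type I error when couples are ignored.** With partner correlation r and split share s, the true variance of the contrast relative to the independence variance is about 1 + f·r·(1 − 2s). At s = 0.5 this is 1. Simulation (12 to 75 couples, r = 0.3 to 0.5) gave a type I error of 0.049 to 0.052. In a single trial s can depart from one half. With f = 0.4 and r = 0.4, s = 1/3 gives 1 + 0.16/3 = 1.05, and s = 2/3 gives 0.95.

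**7. What a couple random intercept buys.** With half the couples split, relative information is (1 − f) + f/(1 − r²). For f = 0.16, r = 0.4: 0.84 + 0.16/0.84 = 1.030, about 3% lower variance. For f = 0.40, r = 0.5: 0.60 + 0.40/0.75 = 1.133, about 12% lower variance.

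**The case against.** Several points on the other side are fair.

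- **The couple share is unknown and may be small.** This stands. At f = 0.16 with half sharing, the loss is about 3 percentage points of power.
- **Sharing is unlikely to be complete.** Accounts are password-protected, and the exercises are the only part described as downloadable. This stands, and makes the full-sharing rows upper bounds.
- **A couple term may exist elsewhere.** The article lists fixed factors only, gives no random-effects structure, and does not reproduce the wording of the registration questions. An analysis plan not shown could include a couple effect. This stands, so the point is that none is stated, not that the model is known to lack one. It does not reach the allocation, which the article fixes and a later analysis plan cannot undo.
- **Dilution runs towards the null in a superiority trial.** True, so it does not threaten a positive result. It does weaken the reading of a null one.

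A reader might also infer that treating partners as unrelated makes the standard error too small and the primary test anti-conservative. That holds for concordant couples alone. Under this scheme split couples offset them on average (step 6). Nor does the design support the inference that nothing can be done later: contact and emergency-contact details are held for every participant, so most couples can probably still be linked.

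**Conclusion.** The point holds as one of undetected contamination. As written, the plan lets both parents enrol, is expected to split half of such couples, and states no means of seeing or examining the effect. Under the assumptions shown, power falls from 0.86 to between 0.83 and 0.80 with 16% of participants in couples, and to between 0.78 and 0.68 with 40%. Each range runs from half to full sharing. These figures rest on an assumed couple share, an assumed degree of sharing, 56 completers per arm and ρ = 0.5. The direction does not depend on those values.

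It is tempting to quote only the worst case, 0.68. That needs both 40% in couples and complete transfer of benefit, and the article supports neither figure. It should not be presented as the expected loss.

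**What to change.** 1. Add a registration item that links parents of the same baby, and store a couple ID. For those already enrolled (62 at the 1 February 2022 status date), assign it from account and emergency-contact details.
2. Add a couple random intercept to the mixed models. This gives a small gain in precision and a standard error that fits the realised mix of concordant and split couples.
3. Pre-specify a sensitivity analysis that excludes split couples or, at the least, control participants whose partner is in the program arm. Keeping only the first-enrolled parent would not serve, because a control whose partner later joined the program arm would stay in.
4. Report the number of couples, concordant and split, by arm.

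The cost is one form item, a linkage exercise and one model term. If couples are few, the couple variance will be poorly estimated.

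Allocating future couples as one unit is optional and a trade-off. It would prevent new splits, but it changes the randomisation mid-trial, cuts across the existing strata and makes the first parent wait for the second. It would also make the couple term necessary, with a design effect of 1 + f × r: about 1.04 (0.2 × 0.2) to 1.16 (0.4 × 0.4).

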#### Safety monitoring

Two primary strategies are in place to monitor participants and ensure their safety throughout the trial. Participant progress will be monitored by the trial clinician to identify elevated distress or risk of harm. The trial clinician [name] is a registered psychologist in Australia with clinical experience in managing perinatal mental health difficulties and diagnoses. Both the participant and the trial clinician will receive automated notification emails if severe symptoms of distress (i.e., total score ≥30 on the K10), depression (i.e., total score ≥13 on the EPDS), or thoughts of self-harm (i.e., item 10 on the EPDS, item 8 on the Perinatal Grief Scale-Short Form (PGS-SF) [43], or item 16 on the Assessment of Quality of Life (AQoL-8D) [44] are indicated at any of the primary timepoints. This notification email will encourage participants to seek support from their support network (e.g., partner, family member) and health professional (e.g., GP/Family Doctor), and if feeling unsafe, to contact emergency or crisis support services. Participants will be contacted by the trial clinician within 72 h via telephone to conduct a risk assessment and determine whether the participant is still eligible to continue in the study, and will be provided assistance to find appropriate support and clinical care if required.

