#### Primary outcome—psychological distress

The Kessler Psychological Distress 10-item scale (K10) [40]—a self-report scale to assess symptoms over the past 4 weeks. Items are rated on a 5-point scale from 1 (none of the time) to 5 (all of the time). In addition to the three primary timepoints, participants in the LWL group will also complete the K10 once per week while completing the intervention to monitor for potential harmful effects of the intervention such as symptom deterioration [45]. The K10 has strong psychometric properties, is sensitive to change (i.e., in tracking symptom changes in response to treatment [46]), and has been used in efficacy studies of digital mental health interventions including perinatal populations [21, 22] and in the context of grief [47, 48].

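### Outcome collection ends at withdrawal or dropout, consent withdrawal is not separated from other stopping, and the text is silent after a post-randomisation eligibility review, which weakens the intention-to-treat analysis of 3-month K10

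*Protocol article*

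**What the plan says.** All references are to the protocol article.

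- **Randomization and allocation procedures:** "No further outcome data will be collected for participants that withdraw or drop out". The terms are not defined there, and nothing is said about people who stop but would still answer questionnaires. The same section provides for staff to contact participants who have been inactive for more than 14 days after an assessment timepoint.
- **Safety monitoring:** the trial clinician is notified of "severe symptoms of distress (i.e., total score ≥30 on the K10"), of a raised EPDS, or of positive self-harm items on three scales, when these "are indicated at any of the primary timepoints". The clinician then telephones to assess risk and to "determine whether the participant is still eligible to continue in the study". The object is the study, and the rule applies to both arms. Whether questionnaires continue after a negative decision is not stated.
- **Data analyses:** "intention-to-treat linear mixed models will be estimated for each outcome measure, with restricted maximum likelihood (REML) estimation used to account for missing data" caused by dropout.
- **Abstract, Methods:** "The primary outcome will be the change in Kessler Psychological Distress Scale (K10) scores from baseline to 3-month follow-up".
- **Participants and recruitment; Sample size calculation:** 75 per arm, allowing for 25% dropout.

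**The concern.** The primary endpoint is a value at 3 months, and the stated rule gives it up for everyone who withdraws or drops out. One route out of the study opens on a high score on the primary outcome scale, so some of the values lost may belong to the participants doing worst. Allocation is open and only the intervention arm has a programme to abandon, so the reasons for leaving may differ between arms.

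A mixed model fitted by REML gives a valid estimate if loss is explained by the data in the model. It cannot use what the clinician heard on the telephone, a participant's unrecorded reason for leaving, or a change after the last completed questionnaire. If loss depends on these, the 3-month contrast can be biased. A sensitivity analysis can then only bound the problem, because the data were never collected.

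**Working it through.** **1. The sections side by side.** Randomization and allocation procedures ends collection at withdrawal or dropout. Safety monitoring allows a participant to be judged no longer eligible for the study and is silent on later questionnaires. Data analyses promises intention-to-treat models and relies on the model for what is missing. Nothing says whether a participant judged ineligible counts as withdrawn. The natural reading is that they do, but that is an inference.

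**2. When the review can cost primary data.** After a 3-month trigger nothing remains to be lost. At baseline, applicants with a K10 of 30 or more have already been interviewed before randomisation (Online screening and enrolment). The main point is therefore post-intervention. A baseline trigger on a self-harm item outside the screener (PGS-SF or AQoL-8D) is also possible, because randomisation follows the baseline questionnaires at once and the call comes within 72 hours.

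**3. The planned loss.** 75 × 0.25 = 18.75, about 19 per arm, leaving 56.25 per arm. I take N = 150 as given. The stated inputs in the repeated-measures formula give 2(1.96 + 0.8416)² × (1 + 2 × 0.5) / (3 × 0.5²) = 41.86, so 42 per arm, 42 / 0.75 = 56 after dropout, and 112 in total rather than 150. That is a separate matter and does not affect this point.

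**4. Simple size of bias.** Let p be the share lost in an arm and δ the amount, in SD, by which their true 3-month K10 exceeds the model's prediction. Bias in the difference has size |p_LWL × δ_LWL − p_CAU × δ_CAU|. The values of δ are assumptions. With p = 0.25 and δ non-zero in one arm only:

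- δ = 0.25: 0.25 × 0.25 = 0.0625 SD, or 12.5% of the 0.5 target
- δ = 0.50: 0.25 × 0.50 = 0.125 SD, or 25% of the target

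If those lost are worse than predicted in LWL only, the benefit is overstated; in CAU only, it is understated by the same amount. With equal p and δ in both arms the bias cancels.

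**5. Which kinds of loss matter.** Large-sample simulation: 400,000 per arm, SD 1, correlation 0.5, true difference −0.50 SD at both follow-ups. Only the 3-month value is lost, and it is predicted from the two earlier scores within arm, as a mixed model would in effect do. Score-driven loss occurs above the upper quartile of the CAU distribution. These mechanisms are assumptions.

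| Loss driven by | Lost CAU / LWL | Mixed-model-type estimate |
|---|---|---|
| Observed post-intervention score, both arms | 25% / 12% | −0.50 (completers only: −0.40) |
| Unseen 3-month score, both arms | 25% / 12% | −0.34 |
| Unseen 3-month score in LWL, random in CAU | 25% / 12% | −0.67 |

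Loss driven by an observed score leaves the planned model unbiased. Loss driven by an unseen score moves the estimate in either direction.

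**6. Precision.** Power = Φ(0.5 × √(n/2) / s − 1.96), two-sided 5% (sidedness is not stated). For a single timepoint or a change score at ρ = 0.5, s = 1; for a baseline-adjusted comparison, s = √(1 − 0.5²) = √0.75. The share that could be retained is not in the document, so the full range is shown.

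| Share of losses retained | n per arm | Single timepoint or change | Baseline-adjusted |
|---|---|---|---|
| None | 56.25 | 75.5% | 86.5% |
| Half | 65.6 | 81.7% | 91.1% |
| All | 75 | 86.5% | 94.2% |

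These count only participants with a 3-month value. A mixed model that also uses post-intervention scores, with half the losses falling before that visit, gives 78.7% and 87.0% at 25% missing, and 83.1% and 91.3% at 12.5% missing.

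**The case against.** Much can be said for the plan, and four stronger readings that a reader might infer do not stand.

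- **That the rule contradicts intention to treat.** It does not. Randomisation follows completion of the baseline questionnaires, so every randomised participant has a baseline K10 and can be analysed in the allocated arm. The article openly says that dropout will be handled by the model. What suffers is the completeness of follow-up.
- **That leaving the programme means leaving data collection.** The text does not say so. Module use is flexible and is measured separately as adherence, questionnaire reminders are not conditional on module use, and staff contact inactive participants. Someone who merely stops opening modules is probably still asked for outcomes. What remains is that dropout is undefined and the no-collection rule has no exception short of consent withdrawal.
- **That high K10 scorers are removed and the result is biased for that reason.** The triggering score at a primary timepoint is observed and enters the model; step 5 shows no bias from loss driven by that score alone. The exposure is to the clinician's further judgement and to later change.
- **That the weekly K10 causes removal in one arm only.** It is true that "participants in the LWL group will also complete the K10 once per week while completing the intervention", but the notification rule under Safety monitoring is tied to the primary timepoints, so the document does not establish this.

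It is also fair that this is a condensed article and that definitions of withdrawal often sit in the full protocol. That would excuse silence, but the no-collection rule is stated outright. Finally, no figure in the document supports differential loss; the bias sizes illustrate and do not predict.

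**Conclusion.** The point holds in a limited form. The article fixes a rule that gives up 3-month K10 values without separating withdrawal of consent to data collection from other stopping, and leaves unclear what happens to questionnaires after an eligibility review. This weakens the intention-to-treat estimate, because the model is exposed to loss that depends on information it does not hold.

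The direction of bias is unknown, so the document does not support a claim that the programme's benefit will be overstated. Under the one-arm assumption at 25% loss the shift is about 0.06 to 0.125 SD; the harsher assumed mechanisms in step 5 move it by about 0.16 to 0.17 SD, one each way. With no bias at all, retaining half of the losses would raise power for the 3-month comparison by about 4 to 6 percentage points. How many people the rule would affect, and how many would still answer, cannot be learned from the document.

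**What to change.** Amend the sentence under Randomization and allocation procedures so that every randomised participant, in either arm, is still invited to the post-intervention and 3-month questionnaires unless they withdraw consent to data collection. Define dropout, and record the reason and date of any stopping separately for the programme and for the questionnaires.

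Reconcile Randomization and allocation procedures, Safety monitoring and Data analyses so that they agree on whether outcomes are sought after an eligibility review. The wording must work for the control arm, which has no programme during the trial. The clinician's decision and its triggers are not in question, and no clinical rule is proposed here.

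The cost is a minor ethics amendment, some extra automated reminders, and possibly more safety telephone calls, since each additional questionnaire can itself trigger one. It would apply mid-trial: 62 had been randomised by 1 February 2022, leaving 150 − 62 = 88 to enrol under the new wording, plus those already enrolled who had not finished follow-up.
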